### Withdrawal or dropout criteria

Participants will withdraw from this trial according to the following:
Participants who decide to withdraw.Development of serious diseases hinders the continuation of the trial.Suffering from a serious adverse event (AE) related to the Tai Chi training.Participations in the waiting list group have regularly engaged in Tai Chi exercise.

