#### Waiting list group

The participants in the waiting list group will be requested to maintain their routine lifestyle and did not take any intervention measures. After the study (24 weeks), participants in the waiting list can choose to participate in Tai Chi training or accept other interventions.

All participants will be informed to record their daily activities or exercise information during the study to observe any effects of normal physical activity.

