### Safety evaluation

During the study intervention, any adverse events of the subject will be monitored, recorded in the adverse event case report form, reported to the research assistant, and analyzed for causality related to Tai Chi training and the severity of the adverse event.

During the intervention, any adverse events (defined as any functional impairment caused by the intervention, such as knee or ankle sprain, increased depression, knee pain, hypoglycemia) will be recorded on the case report form (CRF). If any adverse event occurs, the coaches or project managers will provide the corresponding treatment to the participant. Serious adverse events should be filled in a report form and reported to the Ethics Committee of Fujian University of Traditional Chinese Medicine Subsidiary Rehabilitation Hospital immediately.

Based on various factors, the safety evaluation of the subjects is conducted. The evaluation results are divided into level 1 (safe, without any adverse reactions); level 2 (safer, with mild adverse reactions, no need to do any treatment, subjects can continue to participate in training); level 3 (have safety problems, have moderate adverse reactions, and subjects can continue training after treatment); and level 4 (the study was discontinued due to serious adverse reactions) *(Common Terminology Criteria for Adverse Events (CTCAE) Version 5.0, US Department of Health and Human Services, 2017).*

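### The safety section builds causality into its adverse event definition, against its own recording rule, and assigns treatment of any event, including worsening depression, to coaches or project managers

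*Protocol article*

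**What the plan says.** The first paragraph of Safety evaluation sets a broad rule: "any adverse events of the subject will be monitored, recorded in the adverse event case report form, reported to the research assistant". The events are then to be "analyzed for causality related to Tai Chi training and the severity of the adverse event". No arm is named, and cause plays no part in whether an event is recorded.

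The second paragraph repeats the recording instruction with a definition attached: "any adverse events (defined as any functional impairment caused by the intervention, such as knee or ankle sprain, increased depression, knee pain, hypoglycemia". This is the only explicit definition of an adverse event in the article.

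The second paragraph then says who acts: "If any adverse event occurs, the coaches or project managers will provide the corresponding treatment to the participant". Serious events go on a report form to the ethics committee, again with no arm named.

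The Waiting list group section says that these participants "did not take any intervention measures". The Withdrawal or dropout criteria use the term once, for a participant "Suffering from a serious adverse event (AE) related to the Tai Chi training". The Discussion says the trial observes both effectiveness and safety.

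**The concern.** Whether an untoward event gets onto the form should not depend on a prior opinion about its cause. Where it does, the person deciding whether to record is also deciding relatedness. That person may know the allocation, because coaches and participants are unblinded.

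The listed example that matters most is increased depression. In a trial of subthreshold depression it can occur in either arm without any help from Tai Chi. The Discussion itself raises low mood among controls as a possible confounder. If such worsening counts only when Tai Chi caused it, there is no background rate against which to judge the cases in the Tai Chi group.

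The treatment rule is a participant-care matter. The Inclusion criteria use a diagnostic interview to rule out major depression and significant suicide risk at entry, so the trial already treats these as clinical questions. Yet the article's stated response to worsening during the trial is treatment by a coach or a project manager.

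**Working it through.** The plan gives no figure on this point to reproduce. The check compares the texts and counts participants.

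**Step 1: apply both rules to the same cases.**

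| Case | First paragraph | Second paragraph |
|---|---|---|
| Ankle sprain during a Tai Chi session | Recorded, then assessed (likely related) | Adverse event |
| Depression worsens in the Tai Chi group, judged unrelated | Recorded, then assessed as unrelated | Not an adverse event |
| Depression worsens on the waiting list | Recorded, then assessed as unrelated | Not an adverse event |

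The rules disagree on the second and third cases, which are the ones needed to interpret the first kind.

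**Step 2: test whether the definition can simply be read into the first paragraph.** Suppose it can. Every recorded event is then, by definition, caused by the intervention. The causality assessment in the first paragraph could return only one answer. Reading the paragraphs together makes that step circular, so the conflict remains.

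**Step 3: check the term elsewhere.** The withdrawal criterion qualifies a serious adverse event as one related to the training. That qualifier is needed only if an adverse event can also be unrelated. This section therefore supports the broad meaning.

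**Step 4: count who can have an adverse event.** Inputs: 64 participants, 32 per group (Sample size estimation), and no intervention on the waiting list (Waiting list group).

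- First paragraph: 32 + 32 = 64, and 64/64 = 100%.
- Second paragraph: 32 + 0 = 32, and 32/64 = 50%.

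**Step 5: trace the treatment rule.** The rule applies to any adverse event. Increased depression is on the list of adverse events. It follows that coaches or project managers treat increased depression. The Tai Chi group section describes the coaches as experienced Tai Chi teachers who have had research and human protection training. The project managers' qualifications are not given. Quality control mentions a doctor on its committee but gives that person no part in treating events.

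**The case against.** The strongest reply is that this is one loose parenthesis. Staff who record everything under the first paragraph also capture all that the second requires, so both recording instructions can be obeyed. That is correct as far as it goes, and the documents do not show that waiting-list events will in fact go unrecorded. But the explicit definition is what a site would apply in a doubtful case, and it gives a different answer from the first paragraph.

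Several stronger readings are tempting and are not supported:

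- **That the withdrawal criteria share the narrow meaning.** They point the other way (Step 3). The same list also withdraws participants for serious disease that prevents continuation, with no arm limit, so it needs no change.
- **That a planned comparison of adverse events between arms is lost.** The article states no such comparison. Statistical analyses names the primary and secondary outcomes, and the Discussion speaks of the safety of Tai Chi training. A by-arm table may be in the full protocol or the SAP, which are not shown. What stands is that data recorded under the narrow definition could not supply one.
- **That the Tai Chi group has a calculable excess of contacts.** Both groups keep activity logs, and the waiting list also has entertainment activities whose number is not given. No ratio can be derived.
- **That the safety levels are wrong.** Level 2 reads "with mild adverse reactions, no need to do any treatment, subjects can continue to participate in training" and level 3 reads "have moderate adverse reactions, and subjects can continue training after treatment". These do not fit people who do not train. But they grade adverse reactions, for which that wording is natural, so rewording is optional.
- **That no clinician is involved in the trial.** The project managers may be clinically qualified, and a condensed article may leave referral arrangements to the full protocol. What stands is narrower: the sentence as written lets a coach treat any listed event.

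**Conclusion.** The point holds. Safety evaluation gives two incompatible meanings of adverse event, and the explicit one presupposes the answer that the causality assessment is meant to find. Under it, 32 of 64 participants can have an adverse event instead of 64 of 64, and background worsening cannot be told apart from harm. The same section also assigns treatment of worsening depression to coaches or project managers. Both are stated rules and not details left out of a condensed article.

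The count rests on two assumptions: that the first paragraph, which names no arm, covers both arms, and that waiting-list participants do not take up Tai Chi during the study.

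A reader might infer that the efficacy result is at risk. It is not. PHQ-9, HAMD-17 and CES-D are measured in both groups at weeks 12 and 24, so worsening still shows in the scores, and the sample size is untouched. The effect is confined to the safety data and participant care. It is worth correcting because safety is a stated aim and the correction is cheap.

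**What to change.** In Safety evaluation:

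1. Delete the words in the second paragraph that make causation by the intervention part of the definition.
2. State that adverse events are recorded in both arms regardless of cause, that relatedness to Tai Chi is assessed afterwards as the first paragraph already says, and that counts are reported by arm.
3. Replace the treatment sentence. Coaches give at most first aid, and worsening depression or suicide risk is referred to a qualified clinician. The clinical content of that referral is for the investigators.
4. Optionally, word levels 2 and 3 by whether the participant can continue in the study, so that they also fit people who do not train.

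The cost is a few sentences, one table by arm and slightly more recording on the waiting list, with no added participants or visits. One limit remains: ascertainment may still differ between arms, because the Tai Chi group is seen at supervised sessions.

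### The four-level safety rating ties severity to treatment and to staying in training, so it is not exhaustive and misses non-serious reactions that end training

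*Protocol article*

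**What the plan says.** The Safety evaluation section sets out the rating as follows:

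- The lowest level has a single condition: "level 1 (safe, without any adverse reactions".
- The second joins severity, treatment and continuing: "level 2 (safer, with mild adverse reactions, no need to do any treatment, subjects can continue to participate in training".
- The third joins the same three facts in another combination: "level 3 (have safety problems, have moderate adverse reactions, and subjects can continue training after treatment".
- The highest joins severity to stopping: "level 4 (the study was discontinued due to serious adverse reactions".

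CTCAE version 5.0 is cited at the end of the scale. No rule is given for a reaction that meets some of a level's conditions and not others.

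The same section defines adverse events as "defined as any functional impairment caused by the intervention, such as knee or ankle sprain, increased depression, knee pain, hypoglycemia". On their treatment, a separate sentence adds: "If any adverse event occurs, the coaches or project managers will provide the corresponding treatment to the participant". It also says that events are recorded on a case report form and analysed for causality and severity.

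Two other sections matter here. The Withdrawal or dropout criteria include "Suffering from a serious adverse event (AE) related to the Tai Chi training" and, with no condition on the reason, "Participants who decide to withdraw". The Statistical analyses section keeps in the intention-to-treat population those who leave because of adverse reactions, and sets no severity limit on such departures.

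**The concern.** A rating scale should give every participant exactly one level. Here severity, treatment and training status are three separate facts about an event, but levels 2 and 3 each require a particular combination of all three, and level 4 requires two of them. A participant whose facts do not line up has no level, and the assessor must choose one ad hoc.

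The gaps fall on courses that the document itself foresees. Its examples include knee pain and knee or ankle sprain. Such an event can be non-serious and still be treated or end a participant's training. These cases bear directly on tolerability, yet stopping appears only in level 4, which needs a serious reaction.

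The Discussion names safety, alongside effectiveness, as something the trial sets out to observe. An ad hoc choice between levels 2 and 3 decides whether a participant is labelled as safer or as having a safety problem.

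**Working it through.** The plan gives no figure to reproduce. The check lists the possible courses of an event and matches each to the literal wording.

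**Inputs.** The wording of levels 2 to 4, the adverse event definition and the treatment sentence come from Safety evaluation. The rule on serious related events comes from Withdrawal or dropout criteria. Level 4 is taken to mean that the participant's own participation ends, since the scale rates subjects.

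**Step 1: all combinations.** Severity (mild, moderate, serious) × treated (no, yes) × continues (no, yes) = 3 × 2 × 2 = 12.

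| Severity | Treated | Continues | Level |
|---|---|---|---|
| mild | no | yes | 2 |
| mild | no | no | none |
| mild | yes | yes | none |
| mild | yes | no | none |
| moderate | no | yes | none |
| moderate | no | no | none |
| moderate | yes | yes | 3 |
| moderate | yes | no | none |
| serious | no | no | 4 |
| serious | yes | no | 4 |
| serious | no | yes | not open, see step 2 |
| serious | yes | yes | not open, see step 2 |

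**Step 2: apply the withdrawal criteria.** A serious event related to Tai Chi leads to withdrawal, and adverse events are defined as caused by the intervention. A serious event followed by continued training is therefore not an open course: 12 − 2 = 10 combinations. Of these, 4 have a level and 10 − 4 = 6 do not.

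**Step 3: read *can continue* as ability.** A participant who was able to go on but chose to leave could then be scored in two of the six: mild, untreated, stops (level 2) and moderate, treated, stops (level 3). That leaves 6 − 2 = 4 unscored, all of them mild and treated or moderate and untreated. A participant who was unable to continue stays unscored in those two cells as well. Level 2 speaks of the need for treatment, so its firm gap is a mild reaction that needs treatment.

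**Step 4: apply the treatment sentence literally.** If every adverse event is treated, only the treated rows of the 10 remain: 2 mild + 2 moderate + 1 serious = 5. Two fit (moderate and continuing, level 3; serious and stopping, level 4) and 3 do not. Both mild rows are among the 3, so on this reading level 2 is empty. If the *corresponding* treatment may be none, level 2 is usable and the count returns to step 2.

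**Step 5: score by severity alone.** Mild to level 2, moderate to level 3 and serious to level 4 gives all 10 combinations a level, so 0 are unscored.

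**Scale of one ad hoc choice.** With 32 planned per group (Sample size estimation), one participant is 1/32 = 3.1 percentage points of the Tai Chi group's safety distribution.

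**The case against.** The best defence is that the levels form a severity ladder (none, mild, moderate, serious) and that the clauses on treatment and continuing only describe the usual course at each step. On that reading every event has a level. This is reasonable, and it may be what was meant, but the text does not say so. The clauses stand inside the definitions, and level 4 is worded as discontinuation. Making the ladder explicit is exactly what the fix does.

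A second defence is that form fields and tie-break rules belong in the research manual and case report form. The Quality control section says these will be drawn up, and they are not shown. That would answer a complaint about missing detail. The problem here lies in definitions that the article does state.

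A reader might also infer more than the document supports:

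- **That level 2 can never be assigned.** This holds only if the corresponding treatment always means active treatment. It may mean whatever the event calls for, including nothing, and level 2 refers to need. What stands is a conflict on a literal reading.
- **That 8 of 12 combinations are unscored.** Two of those are serious events followed by continued training, which the withdrawal criteria close.
- **That the unscored courses are common, or would affect a given number of participants.** The document gives no adverse event rates. Its 10% dropout allowance is not attributed to adverse events.
- **That these levels are the only safety summary.** Severity and causality are also analysed per event, and serious events have their own report form. A misassigned level would not erase the event record.

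**Conclusion.** The point stands as a limited defect in a stated rule. The rating is not exhaustive: 6 of the 10 open combinations have no level on a literal reading, and 4 if *can continue* means ability and the participant leaves by choice. Even on the ability reading, a mild reaction that needs treatment and a moderate one after which training cannot resume match no level. Because the only level that includes stopping requires a serious reaction, the rating does not capture non-serious events that end training, although the withdrawal criteria and the Statistical analyses section allow for them. Separately, the treatment sentence and level 2 must be reconciled.

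These counts are of types of course, not of participants, and how many participants would be affected cannot be estimated from the document. They assume that a level's conditions apply jointly; if only severity was meant to count, the remedy is to say so. The consequence is confined to safety classification and reporting. Efficacy analysis, sample size and error rates do not change.

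**What to change.** In Safety evaluation:

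1. Derive the four levels from severity alone and state which CTCAE 5.0 grades correspond to each level. CTCAE is already cited, and severity is already assessed per event.
2. Record two further items per event on the case report form: whether treatment was given, and whether training continued, was paused or was stopped.
3. Report each participant's worst level and, separately, the number who stop training because of any adverse event, whatever its severity.
4. Reconcile the sentence on treating any adverse event with the wording of level 2. Which of the two should change is a clinical matter for the investigators; no treatment or stopping rule is proposed here.

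The cost is a few more fields per event and one more table row, with no extra visits, staff or procedures.

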### Data collection and management

The evaluator used a paper case report form (p-CRF) to collect data. The research assistant conducted quality control of the data collection and input this data into the Microsoft Office Excel (Microsoft, USA). All data entered into the Excel were imported into the data management platform (FJTCM yun) at http://10.252.47.2 and managed by an independent organization. All data were treated with the highest confidentiality.

When participants withdrew from a trial, the investigator asked the participant whether the participant was willing to participate in follow-up data collection; if the participant was willing, every effort would be made to obtain the follow-up data.

### Statistical analyses

Analysis of all data in this trial was performed by an independent statistician who is not involved in the evaluation of the results using the SPSS V.24.0 software package, with a statistical significance of a two-sided *p* value less than 0.05. Normally distributed continuous variables were described as mean ± standard deviation (SD), and non-normal variables were described as the median and interquartile range (IQR). Categorical variables were reported as frequencies or percentages. In this study, basic data including age, gender, BMI [49], education level [50], family factors [51], economic ability [52], and screen time [7] were collected, and basic data were proposed as covariates in this study. Analysis of the primary and secondary outcomes was performed based on the intention-to-treat (ITT) population and per-protocol (PP) population. The result of the ITT analysis was compared with that of the PP analysis to determine whether the results are consistent. Multiple imputations were used to impute missing data. ITT analysis was performed on all subjects in the Tai Chi group and waiting list group. In this study, after the subjects were randomly divided into groups, regardless of whether they received the treatment of the group, they were eventually included in the assigned group for statistical analysis, even though they withdrew from the trial due to adverse reactions. Differences between groups in the Tai Chi group and the waiting list group at each time point (12 weeks after intervention or 12 weeks’ follow-up) were analyzed using Student’s *t* test or Mann-Whitney *U* test. The interaction effect of group × time was analyzed by the linear mixed model with restricted maximum likelihood. Pearson correlation or Spearman correlation was adopted for correlation analysis.

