### Sample size estimation

In this study, the influence of Tai Chi on the depressive symptom of young adults with subthreshold depression was observed. When estimating the sample size, PHQ-9 and HAMD-17 were used as the main effect indicators to calculate the required sample size. Besides, the larger sample size was used as the sample size of this study.

The sample size estimation was based on the improvement in PHQ-9 (The 9-item Patient Health Questionnaire) scores. According to relevant published literature [22], the mean and its SD of PHQ-9 scores after the 8 weeks of mindfulness-based Tai Chi training for subthreshold depression adolescents were 6.03 and 2.18 points, respectively, while the mean and its SD of PHQ-9 scores in the control group were 8.10 and 2.52 points, respectively. According to the above results, a sample size of 58 participants was calculated to sufficiently detect the target effect size (0.879) with a type 1 error of 5% (*α* = 0.05) and 90% power (*β* = 0.10) by Gpower V.3.1.9.2 software. Assuming a dropout rate of 10%, a total of 64 participants are necessary, with 32 participants in each group.

Simultaneously, according to the research [21], the total score of HAMD-17 obtained by regular Tai Chi training to improve patients with major depressive disorders was 9 ± 5 points while the HAMD-17 score of control group patients with major depressive disorders was 15 ± 7 points. Based on the above results, a sample size of 46 participants was calculated to sufficiently detect the target effect size (0.986) with a type 1 error of 5% (*α* = 0.05) and 90% power (*β* = 0.10) by Gpower V.3.1.9.2 software. Assuming a dropout rate of 10%, a total of 52 participants are necessary, with 26 participants in each group.

Since the sample size calculated using PHQ-9 as the result indicator is more than HAMD-17, this study chose PHQ-9 as a basis to estimate the sample size of this study, and a total of 64 subjects were recruited.

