#### Primary outcome measures

The primary outcome measure changes in the PHQ-9 and HAMD-17 between baseline and 12 weeks.

The 9-item Patient Health Questionnaire (PHQ-9) is a self-report measure used to assess 9 depressive symptoms according to the DSM-IV depression criteria. It has a total of 9 items, each with a score of 4 points (0–3 points) and the total scores’ range of 0–27 points. This score can be used to describe the patient’s symptoms, divided into five categories: none (0–4), mild (5–9), moderate (10–14), moderately severe (15–19), and severe (20–27) [41]. PHQ-9 has been translated into Chinese, and its Chinese version has demonstrated reliability and validity [42].

The 17-item Hamilton Depression Scale (HAMD-17) [43] is the most widely used scale in the clinical evaluation of depression, including17 items that assess function in five areas: anxiety/somatization, retardation, cognitive impairment, sleep disturbance, and weight change. Higher scores indicate more severe depression.

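### The named 12-week comparison is unadjusted and the baseline PHQ-9 and HAMD-17 scores are not listed as covariates, so available precision is given up; the stated 90% power holds for the 12-week score, and for change only if the baseline-to-week-12 correlation is about 0.5 or more

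*Protocol article*

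**What the plan says.** Four statements in the protocol article bear on this point.

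- **Endpoint.** Under Primary outcome measures: "The primary outcome measure changes in the PHQ-9 and HAMD-17 between baseline and 12 weeks". The abstract says the same.
- **Test.** Under Statistical analyses, "Differences between groups in the Tai Chi group and the waiting list group at each time point" are assessed by Student's t test or the Mann-Whitney U test. The section does not say whether the variable tested is the score at that visit or its change from baseline. The next sentence adds a REML linear mixed model for the group × time interaction. Neither analysis is named as primary.
- **Covariates.** After listing seven items (age, gender, BMI, schooling, family and economic circumstances, screen time), the section says "basic data were proposed as covariates in this study". Baseline PHQ-9 and HAMD-17 are not in the list, and the list is not tied to any model. Both scores are measured before randomisation.
- **Sample size.** The Sample size estimation section starts from "the mean and its SD of PHQ-9 scores after the 8 weeks of mindfulness-based Tai Chi training", that is, from post-treatment scores. The inputs are "mindfulness-based Tai Chi training for subthreshold depression adolescents were 6.03 and 2.18 points, respectively" and, for comparison, "the mean and its SD of PHQ-9 scores in the control group were 8.10 and 2.52 points, respectively".

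**The concern.** The endpoint, the test and the basis of the power calculation do not refer clearly to the same quantity. The endpoint is change, the sample size is built on scores after treatment, and the test could be on either.

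Whichever is meant, neither a t test nor a Mann-Whitney test can take a covariate. The baseline value of the outcome, usually the strongest predictor of its later value, is therefore either ignored (test on score) or subtracted with a fixed coefficient of one (test on change). ANCOVA estimates that coefficient from the data and, apart from one degree of freedom, is at least as precise as both.

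Two things are at stake. The first is precision in a small trial. The second is whether the 90% power quoted for the trial belongs to its declared endpoint. With about 29 evaluable participants per arm, chance baseline differences are also not negligible, and an unadjusted estimate carries part of them.

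**Working it through.** **Inputs.** From Sample size estimation: PHQ-9 means 6.03 and 8.10, SDs 2.18 and 2.52, alpha 0.05, power 90%, 58 evaluable participants (29 per arm). The two-sided level is from Statistical analyses. The correlation r between baseline and week 12 is not in the document, so a range is assumed. Baseline and week-12 SDs are taken as equal unless stated.

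**Step 1: reproduce the plan's figure.** Pooled SD = √((2.18² + 2.52²)/2) = √5.5514 = 2.356. Standardised difference d = (8.10 − 6.03)/2.356 = 2.07/2.356 = 0.879, as stated. A two-sided two-sample t test (noncentral t) needs 29 per arm, 58 in total, with power 90.8%. This reproduces. The HAMD-17 figure also reproduces: d = 6/6.083 = 0.986, 23 per arm, 46 in total, power 90.5%.

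The stated 90% is therefore the power of an unadjusted t test on the post-treatment score. It does not depend on r. With a Mann-Whitney test (relative efficiency 0.955 under normality) it is about 89.5%.

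**Step 2: other analyses of PHQ-9 at 29 per arm.**

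- Unadjusted change: SD = σ√(2(1 − r)), so the effective d is 0.879/√(2(1 − r)).
- ANCOVA on baseline: residual SD = σ√(1 − r²), so the effective d is 0.879/√(1 − r²), with one further degree of freedom used.

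| Assumed r | 12-week score, unadjusted | Change, unadjusted | ANCOVA |
|---|---|---|---|
| 0.3 | 90.8% | 79.4% | 93.1% |
| 0.4 | 90.8% | 85.1% | 94.8% |
| 0.5 | 90.8% | 90.8% | 96.7% |
| 0.6 | 90.8% | 95.7% | 98.4% |
| 0.7 | 90.8% | 98.9% | 99.6% |

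Example at r = 0.3: change, 0.879/√1.4 = 0.743; ANCOVA, 0.879/√0.91 = 0.921.

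Participants per arm for 90% power, change against ANCOVA: 40 against 26 (r = 0.3), 29 against 22 (r = 0.5), 18 against 15 (r = 0.7).

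**Step 3: break-even for change.** Change has the same SD as the score when 2(1 − r) = 1, that is r = 0.5. If the baseline SD is k times the week-12 SD, the variance of change is σ²(1 + k² − 2rk), and break-even moves to r = k/2. At r = 0.3, power for change is 79.4% with k = 1, 86.3% with k = 0.8 and 90.8% with k = 0.6.

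**Step 4: HAMD-17.** With d = 0.986 and 29 per arm, unadjusted change has power 87.7%, 92.1% and 95.8% at r = 0.3, 0.4 and 0.5. The shortfall is smaller than for PHQ-9 because the trial is sized on PHQ-9.

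**Step 5: chance imbalance.** The standard error of the baseline difference is √(2/29) = 0.26 SD, so a difference above 0.25 SD in either direction arises in about one trial in three. Given such an imbalance and r = 0.5, an unadjusted estimate on either scale is shifted by 0.5 × 0.25 = 0.125 SD, or 0.125 × 2.356 = 0.29 PHQ-9 points, against a planned difference of 2.07.

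**The case against.** A reader might infer that the t test is on change, that leaving out the baseline score undoes the stated power, and that the analysis is therefore wrong. The document does not support this.

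- It does not say that change is tested. A comparison at each visit fits a test on scores at least as well, and on that reading the sample-size calculation matches the test at 90.8%.
- The 90% never assumed adjustment, so omitting baseline cannot remove it. The difference between endpoint (change) and sizing (score) is a separate matter, and it reduces power only if r is below about 0.5. No r is given. Above 0.5 a change analysis exceeds the stated power.
- Restricted entry might lower r, but screening is on CES-D and the absence of major depression, not on PHQ-9 or HAMD-17. Any restriction would also shrink the baseline SD, which lowers the break-even point (step 3).
- Under randomisation, unadjusted comparisons of scores or of change are valid and, over repeated trials, unbiased.

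All of this stands.

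The remaining defence is that the planned mixed model already uses the baseline score, and that covariate detail can be left to an analysis plan that is not shown. This stands only in part. The model is not named primary, and the text does not say whether baseline is one of its time points. If it is, with freely estimated group means at baseline, an unstructured covariance and complete data, the week-12 group × time contrast is simply the difference in mean change. It then depends on r exactly as the change analysis does, and the gain from ANCOVA remains. As for detail left to an analysis plan, the article itself names the tests, lists the covariates and states the power basis, so their fit with one another can fairly be judged here.

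**Conclusion.** The point holds as a loss of precision and an unclear match between endpoint, test and power statement. It does not hold as an error that invalidates the primary comparison.

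For PHQ-9 at 29 per arm, ANCOVA raises power over the unadjusted 12-week score by 2.3 points at r = 0.3 (93.1% against 90.8%), 5.9 at r = 0.5 and 8.8 at r = 0.7. Over unadjusted change the gain is 13.7 points at r = 0.3, 5.9 at r = 0.5 and 0.7 at r = 0.7. ANCOVA is the only one of the three that is above 90% for every r in this range and never the weakest.

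The stated 90% is correct for the 12-week score. For unadjusted change it is correct only if r is at least about 0.5. These figures assume normal data, equal baseline and week-12 SDs, the planned PHQ-9 effect, and values of r that the protocol does not supply. Whether power for change actually falls short cannot be settled from the document.

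**What to change.** - **Statistical analyses.** Name one primary analysis for each primary outcome: ANCOVA of the week-12 score on group, with the baseline value of the same score as covariate, reporting the adjusted mean difference with its 95% confidence interval. An equivalent baseline-adjusted mixed model would also serve, with its week-12 contrast specified. Keep the t and Mann-Whitney tests as supportive. With baseline as covariate, analysing the week-12 score or the change gives the same group effect, so the declared endpoint need not be altered.
- **Sample size estimation.** State that 58 evaluable participants give about 90% power for the unadjusted 12-week PHQ-9 score, more with baseline adjustment, and 90% for unadjusted change only if the baseline-to-week-12 correlation is at least about 0.5.

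The cost is wording and one degree of freedom. No extra participants or measurements are needed, since both baseline scores are already collected. The change should be made before unblinding, so that the choice between the listed analyses cannot depend on the results.
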